## Results

Recruitment will start in June 2023, and data collection is expected to end in 2024. Results are expected to be available in January 2025. We also intend to make publications available in 2025, and the results of our trial will also be presented at conferences.

## Discussion

### Overview

In light of the possible role of glutamatergic signal dysregulation in OCD, it is possible to find, among glutamatergic drugs, candidates for an OCD therapy augmentation strategy.

This has motivated the use of glutamate modulators in patients who are unresponsive to standard pharmacotherapeutic approaches. Several RCTs that used glutamate-modulating agents, such as memantine, riluzole, N-acetylcysteine, and glycine, reported promising benefits [38,54,55]. In particular, 4 RCTs were conducted that used memantine (vs a placebo) as an augmentative agent to SRIs in the treatment of moderate to severe OCD [56].

Marinova and colleagues [39] reported that memantine was the compound that most consistently showed a positive effect, as an augmentation medication, on OCD in their study. A critical letter [40] exposed some concerns on this conclusion and proposed that, in light of some methodological gaps, it is necessary to conduct more studies on the use of memantine as an OCD augmentation therapy.

### Limitations

Our outpatient clinic—a center specializing in OCD—is an academic service of the Department of Human Neurosciences, Sapienza University of Rome. This could represent a limitation—patient selection bias—due to patients’ access to the center’s services. Moreover, our study will use a small sample size due to the limits of service access and the inclusion criteria.

### Conclusion

To the best of our knowledge, only 4 RCTs have been conducted in recent years that investigated the effects of memantine in patients with refractory severe OCD; our trial will be the first one of its kind in Italy. The innovation of this research proposal is not limited to the evaluation of the efficacy and safety of memantine as an augmentation medication for OCD. Through slow titration and follow-up, we will also observe the minimum effective dose of memantine and its residual efficacy after drug withdrawal by using an 8-week follow-up procedure. In addition, by measuring potential executive function impairments during the study period, we might confirm whether memory and attention are modulators of overall clinical improvement. In other words, we will test if memantine, being an antiglutamatergic agent, acts as a pure antiobsessive medication or if memantine’s ability to improve concentration and attention mimics an antiobsessive effect.

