**Results:**

Recruitment has not yet started. The study will be conducted from June 2023 to December 2024. Results are expected to be available in January 2025. Throughout the slow-titration period, we will observe the minimum effective dose of memantine, and the follow-up procedure will detail its residual efficacy after drug withdrawal.

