### Interventions

This is a protocol for a double-blind, randomized, parallel-group, placebo-controlled, monocenter trial in patients with OCD. The trial will include 1 active memantine dose arm and 1 placebo arm.

The trial will consist of the following four distinct periods:

Screening: the screening period may last up to 4 weeks for each eligible patient.A 32-week, double-blind, up-titration treatment period (from T0 to T4): after screening, patients who meet all eligibility criteria will be randomly assigned to 1 of 2 arms (memantine or placebo) in a 1:1 ratio. Following baseline assessments, each patient will receive a daily dose of memantine or the placebo (up to 20 mg/day).An 8-week, double-blind, down-titration treatment period (from T4 to T5): at T4, the dose of memantine or the placebo will be reduced to 10 mg per day due to safety reasons, before the end of treatment (T5).Follow-up period (from T5 to T6): after the 40-week, double-blind treatment period, patients will be asked to come back for the follow-up visit (T6) 8 weeks after the end of the treatment (T5; Figures 2 and 3).

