### Sample Size

The sample size was calculated by using the G*Power 3.1.9.2 software (Heinrich-Heine-Universität Düsseldorf) [53]. By using the ANOVA repeated measures test with a within-between group interaction approach (considering changes in Y-BOCS scores as the primary outcome), an α of .5, a power (1 − β) of 0.85, 2 groups (SSRI and memantine group vs SSRI and placebo group), and 7 measurements (T0 to T6); and by assuming a correlation of 0.5 among repeated measures and a nonsphericity correction ε of 1, we determined that a total sample size of 20 participants (10 in each group) will be necessary to achieve a moderate effect size (*f*=0.25).

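### The article promises to observe memantine's minimum effective dose, but a single up-titrated arm ties dose to time on drug and can at best bound it, unreliably with 10 per arm

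*Protocol article*

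**What the plan says.** The claim appears twice in the protocol article, each time without qualification. Under Results in the abstract: "Throughout the slow-titration period, we will observe the minimum effective dose of memantine". Under Conclusion in the Discussion: "Through slow titration and follow-up, we will also observe the minimum effective dose of memantine". In both places the same sentence goes on to residual efficacy after withdrawal, which is a separate matter.

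The design is under Interventions: "The trial will include 1 active memantine dose arm and 1 placebo arm", and "patients who meet all eligibility criteria will be randomly assigned to 1 of 2 arms (memantine or placebo) in a 1:1 ratio". The dose is raised from T0 to T4 (32 weeks) to a ceiling of 20 mg/day. Then "at T4, the dose of memantine or the placebo will be reduced to 10 mg per day due to safety reasons", which lasts 8 weeks, to T5. T6 follows 8 weeks after treatment ends. The individual dose steps are not in the readable text, and the timeline figure is not shown.

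Under Sample Size, "a total sample size of 20 participants (10 in each group) will be necessary", a figure reached "by assuming a correlation of 0.5 among repeated measures". Statistical Methods plans a repeated measures ANOVA of Y-BOCS and descriptive statistics at each time point. The minimum effective dose is not among the three aims under Objectives. Limitations mentions patient selection and the small sample, but not the link between dose and duration.

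**The concern.** A minimum effective dose is a statement about what a lower dose would have done. To learn it, some patients must stay on the lower dose for as long as others take the higher one. Here every patient in the memantine arm moves up together, so each higher dose also comes with longer exposure. The placebo arm removes natural course and placebo response, but it does not remove time on drug. If the arms first separate at some visit, a lower dose held for the same time might have done as well.

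The 10 mg step does not break the tie, because everyone reaches it after the up-titration. Benefit kept there may be carry-over. Benefit lost there points to a need for more than 10 mg, but only if there is no carry-over or tolerance.

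At stake is how the result is read. A clinician could take the dose at first separation as the dose a patient needs.

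**Working it through.** **The plan's own figure.** The article gives no number for the minimum effective dose. Its only related figure is the sample size. For the within-between interaction, λ = f²·N·m·ε/(1−ρ) = 0.25²×20×7×1/0.5 = 17.5, with 6 and 108 degrees of freedom. At two-sided 5% this gives power 0.881; N = 18 gives 0.836. So 20 is reproduced at α = .05, the level used in Statistical Methods. (Sample Size prints α as .5, which is a separate matter.) That calculation concerns the group-by-time interaction and says nothing about locating a dose.

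**Step 1: what the design can identify without sampling error.** Assumptions, none of them in the article:
- a threshold dose D;
- a lag of 8, 16, 24 or 32 weeks at or above D before benefit shows;
- carry-over of 0, 8 or 16 weeks;
- two illustrative step schedules for T1/T2/T3/T4.

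Visits are 8 weeks apart (32 weeks over T0 to T4), and T5 is at 10 mg. The doses compatible with each pattern are:

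| First separation | 5/10/15/20 mg | 10/10/20/20 mg |
|---|---|---|
| T1 | 5 | 10 |
| T2 | 5 or 10 | 10 |
| T3, kept at T5 | 5, 10 or 15 | 10 or 20 |
| T3, lost at T5 | 15 | 20 |
| T4, kept at T5 | 5, 10, 15 or 20 | 10 or 20 |
| T4, lost at T5 | 15 or 20 | 20 |

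When benefit is kept, the dose at first separation is the largest compatible dose, hence an upper bound. Some patterns leave a single dose, but only on the assumed grid. At T1 it is simply the lowest dose tried. At T3 lost under the first schedule it means above 10 and at most 15 mg, given no carry-over. If the lag is fixed at 8 weeks, each visit maps to one dose, so the identification comes from the assumed lag.

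**Step 2: precision at one visit.** With n = 10 per arm and ρ = 0.5 (both from Sample Size), the SD of change from baseline is √(2(1−0.5)) = 1 raw SD. The 95% half-width is t(0.975, 18)×√(2/10) = 2.101×0.447 = 0.94 SD.

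**Step 3: where first separation falls.** This is a simulation of 200,000 trials per setting. It uses compound symmetry, a two-sample t test on change from baseline at each of T1 to T4, and two-sided p < .05 in favour of memantine. The test and the effect sizes are assumptions.

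If the first step already has its full, constant effect (true visit T1):

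| Effect | At T1 | At T2–T4 | At none of T1–T4 | Late, among those that separate |
|---|---|---|---|---|
| 0.5 SD | 18% | 24% | 58% | 57% |
| 0.8 SD | 40% | 32% | 29% | 44% |
| 1.0 SD | 56% | 29% | 15% | 34% |

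The T1 column agrees with exact noncentral-t power at one visit (0.184, 0.395, 0.562).

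If the effect begins later, among trials that separate by T4:

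| True visit | Effect | Early | Late |
|---|---|---|---|
| T3 | 0.5 SD | 15% | 33% |
| T3 | 0.8 SD | 8% | 28% |
| T3 | 1.0 SD | 6% | 23% |
| T4 | 0.5 SD | 30% | not possible by T4 |
| T4 | 0.8 SD | 16% | not possible by T4 |
| T4 | 1.0 SD | 11% | not possible by T4 |

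Sampling error therefore moves first separation in both directions. An early separation names a dose below the true one, and the upper bound then fails.

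**The case against.** The strongest reply is that little hangs on the claim. It is absent from the aims, the interventions, the sample size and the statistical methods. The verb is *observe*, which can be read as descriptive. No endpoint, test or patient's treatment depends on it. That stands, and it makes the point minor.

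A second reply is that the percentages rest on steps, lags, carry-over, effect sizes and a visit-by-visit test that the article does not state. That also stands. They are illustrations only. The confounding argument needs none of them, only the single up-titrated arm. A separate analysis plan could not cure it either, since no analysis can separate dose from duration here without assuming the lag.

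Two stronger readings are tempting, and neither is supported. A reader might infer that first separation always tends to come too late and so overstates the dose. The first table under Step 3 shows only lateness because it places the effect at T1; the second shows early separation too. A reader might also infer that the 10 mg step can teach nothing. Under some assumed schedules, loss of benefit there leaves one compatible dose, so the accurate statement is that it helps only under assumptions about carry-over and tolerance.

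**Conclusion.** The concern holds as a minor point of wording. The abstract and the Conclusion claim a property that the design lacks. Without sampling error and under a threshold model, the dose at first separation is an upper bound on the minimum effective dose. Loss of benefit at 10 mg could add a lower bound if there is no carry-over or tolerance. Naming one dose requires assumed steps, lag and carry-over. With a half-width of 0.94 SD at one visit, even the bound is unreliable in either direction.

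The half-width rests on the article's 10 per arm and correlation of 0.5; the simulated percentages also rest on the assumptions listed with them. A reader might infer that the efficacy result is compromised. It is not: the primary memantine-placebo comparison does not use the dose at each visit.

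**What to change.** In the abstract's Results and in the Conclusion, replace only the minimum-effective-dose clause with:

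> We will describe, as exploratory, the memantine-placebo difference in Y-BOCS with 95% CI at T1–T5 alongside the dose at each visit; because dose rises with time on drug and the 10 mg step follows the up-titration, these differences reflect dose and duration combined and will not be read as identifying a minimum effective dose.

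Keep the residual-efficacy clause (T6) as it stands in both sentences.

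The cost is two edited clauses. Descriptive statistics at each time point are already planned, so only the confidence intervals and a dose column are added. The downside is that one side deliverable is downgraded. Answering the dose question properly would need randomised fixed-dose arms, which 20 participants cannot support.

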**Conclusions:**

The innovation of this research proposal is not limited to the evaluation of the efficacy and safety of memantine as an augmentation medication for OCD. We will also test if memantine acts as a pure antiobsessive medication or if memantine’s ability to improve concentration and attention mimics an antiobsessive effect.

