### Objectives

The main purpose of our study is to conduct a double-blind, randomized, parallel-group, placebo-controlled, monocenter trial to assess the efficacy and safety of memantine—a low- to moderate-affinity, noncompetitive N-methyl-D-aspartic acid receptor antagonist [40] that is currently approved for the treatment of Alzheimer disease—as an augmentative agent to an SSRI in the treatment of moderate to severe OCD. The second aim of the study is to evaluate the effect of memantine on the concentration and attention abilities of patients with OCD. The third aim is to investigate if responses to memantine could be modulated by variables such as gender, symptoms subtypes, and the duration of untreated illness.

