### Trial Design

A double-blind, randomized, parallel-group, placebo-controlled, monocenter trial will be conducted over 52 weeks at the outpatient clinic of the Department of Human Neurosciences, Sapienza University of Rome. The study population will include patients diagnosed with moderate to severe OCD according to the diagnostic criteria of the DSM-5 who consecutively access the OCD outpatient clinic of the Department of Human Neurosciences, Sapienza University of Rome. The investigators will be academic research assistants and psychiatrists with experience in OCD.

We will enroll patients who meet the diagnostic criteria of the DSM-5 [12] for moderate to severe OCD, and those with a Yale-Brown Obsessive Compulsive Scale (Y-BOCS) [42] score of >21 will be selected for inclusion in the study. The Y-BOCS, which will be used to evaluate treatment efficacy, is a well-validated, 10-item rating scale that is widely used to measure the severity of OCD symptoms. Participants will be rated with the Y-BOCS at baseline and at 2, 4, 6, 8, 10, and 12 months.

During the screening period and T4 and T6 follow-up visits, all participants will undergo an extensive neuropsychological evaluation. We will assess processing speed by using the Wechsler Adult Intelligence Scale, Fourth Edition, Digit Span [43]; attention by means of the Trial Making Test [44]; computerized alertness and go/no-go task memory by using the Digit and Corsi Span [45], a modified version of the Corsi Block-Tapping Test [46], the story recall portion of the Rivermead Behavioral Memory Test [47], and a modified version of the Babcock Story Recall Test [48]; and executive functions by means of the Stroop task [49], a modified version of the Tower of London test [50], and the Modified Five-Point Test [51].

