### Statistical Methods

Descriptive statistics for baseline characteristics and the measurements at each time point will be calculated. For the primary objective, a repeated measures ANOVA approach will be used to detect between- and within-group differences in Y-BOCS variables. *P* values of <.05 will be considered statistically significant. Data will be analyzed by using SPSS version 20 (IBM Corp).

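### The promised test of whether memantine acts directly on OCD or only through better attention cannot be delivered by one on-treatment cognitive assessment in 20 patients

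*Protocol article*

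**What the plan says.** The mechanistic promise appears twice. The abstract's Conclusions say "We will also test if memantine acts as a pure antiobsessive medication" or whether improved concentration and attention imitate such an effect. The Discussion's Conclusion first puts it more softly, "we might confirm whether memory and attention are modulators of overall clinical improvement", and then restates it firmly: "we will test if memantine, being an antiglutamatergic agent, acts as a pure antiobsessive medication".

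The cognitive schedule is in Trial Design: "During the screening period and T4 and T6 follow-up visits, all participants will undergo an extensive neuropsychological evaluation". The same section has the Y-BOCS rated at baseline and at months 2, 4, 6, 8, 10 and 12.

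Interventions fixes the patient's treatment status at each visit. There is "A 32-week, double-blind, up-titration treatment period (from T0 to T4"; then "at T4, the dose of memantine or the placebo will be reduced to 10 mg per day". Treatment ends at T5, and T6 follows 8 weeks later.

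Sample Size arrives at 20 patients, 10 per arm, for the group-by-time interaction in Y-BOCS over seven measurements. Statistical Methods names one analysis, the repeated measures ANOVA of Y-BOCS, followed by the general sentence that P "values of <.05 will be considered statistically significant".

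**The concern.** Whether better attention accounts for the fall in Y-BOCS is a question of mediation, although the Conclusion speaks of modulators. To answer it, the trial must show that memantine changes attention, that this change comes before the symptom change or can otherwise be separated from it, and that little or no treatment effect remains once attention is accounted for.

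The schedule gives one attention value on treatment, taken at the same visit as the outcome. The sample was not sized for any cognitive question. Two wrong readings are then likely. If no cognitive difference reaches significance, the result may be reported as a direct antiobsessive action. If one does, it may be reported as the mechanism. The data would support neither. The schedule and the sample size are fixed in the protocol, so no analysis plan can remove the problem.

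**Working it through.** **1. What is measured when** (Trial Design, Interventions; T0 to T6 matched to the seven Y-BOCS ratings)

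| Visit | Y-BOCS | Cognition | Treatment status |
|---|---|---|---|
| Screening / T0 | yes (baseline) | yes (screening) | before treatment |
| T1 to T3 (months 2, 4, 6) | yes | no | up-titration period |
| T4 (month 8) | yes | yes | end of the up-titration period |
| T5 (month 10) | yes | no | end of the reduced-dose period |
| T6 (month 12) | yes | yes | 8 weeks off treatment |

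Of three cognitive assessments, one is on treatment. Three post-baseline Y-BOCS ratings precede it and one coincides with it. The later two fall at the end of dose reduction and after withdrawal.

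**2. The plan's own sample size**

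For the within-between interaction, λ = f²·N·m·ε/(1 − ρ), with df (k − 1)(m − 1)ε and (N − k)(m − 1)ε. Inputs from Sample Size: f = 0.25, ρ = 0.5, ε = 1, k = 2, m = 7. Alpha is printed as .5. Taking it as .05:

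- N = 20: λ = 0.0625 × 20 × 7/0.5 = 17.5, df 6 and 108, power 0.881.
- N = 18: power 0.836, below the target of 0.85.

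So 20 is reproduced for Y-BOCS at .05. At .5 the answer would be 8, so the printed alpha looks like a misprint.

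**3. The same formula on the cognitive schedule, N = 20**

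- Three measurements: λ = 0.0625 × 20 × 3/0.5 = 7.5, df 2 and 36, power 0.65. Reaching 0.85 needs 32 patients.
- Screening and T4 only: λ = 0.0625 × 20 × 2/0.5 = 5, df 1 and 18, power 0.56. Reaching 0.85 needs 38.

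With two measurements, λ = 5 equals d²·n/2 with n = 10 and d = 1.0. At ρ = 0.5, the plan's moderate f therefore already stands for a between-arm difference in change of a full SD.

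**4. Between-arm difference at T4 in one cognitive measure, 10 v 10**

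Noncentrality d·√(10/2), df 18, two-sided .05, critical t 2.101:

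- d = 0.5: noncentrality 1.118, power 0.19.
- d = 0.8: noncentrality 1.789, power 0.40.
- d needed for 85% power: 1.42. If adjusted for a screening value correlated 0.5 or 0.7 with T4 (assumed), about 1.23 or 1.01.
- Half-width of the unadjusted 95% interval: 2.101 × √(2/10) = 0.94 SD.

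**5. Mediation itself** (simulation; assumed paths; both arm-to-attention and attention-to-Y-BOCS given arm must reach P<.05)

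| Arm effect on attention (SD) | Attention to Y-BOCS path | Power at N = 20 | N for 80% |
|---|---|---|---|
| 0.5 | 0.3 | 0.04 | about 144 |
| 0.8 | 0.5 | 0.23 | about 56 |
| 1.2 | 0.59 | 0.56 | not computed |

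A larger trial on the same schedule would not settle direction. Data were simulated with symptom change driving attention (arm effect on Y-BOCS 1.0 SD, correlation 0.5). The joint test then wrongly pointed to mediation in 10% of trials at N = 20 and 94% at N = 200.

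**6. Several tests (conditional)**

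Trial Design can be read as naming 12 tests. If each were judged at P<.05 at T4, the chance of at least one false positive would be 1 − 0.95¹² = 0.46 under independence. It would be 0.40, 0.32 and 0.23 for assumed between-test correlations of 0.3, 0.5 and 0.7.

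**The case against.** **Softer wording exists.** The sentence before the claim only hopes to confirm something, and Limitations admits a small sample. This stands, but the Conclusion then restates the hope as a test, the abstract has no softer version, and Limitations does not tie sample size to the mechanistic claim.

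**Temporal order is not wholly absent.** T4 attention could be related to Y-BOCS at months 10 and 12. True, but those ratings fall in dose reduction and withdrawal, so they cannot show what produced the improvement while the dose was being raised.

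**Multiplicity may be settled elsewhere.** A reader might infer that every cognitive test will be judged at .05 and that a chance finding is likely. The documents do not say so. The threshold stands beside the Y-BOCS analysis alone, and a key cognitive measure or an adjustment may be in the analysis plan, which is not shown. The count of 12 is also only one reading, since digit span and Corsi tasks each appear twice. The risk is below one half even under independence, and tests from one battery are probably correlated. Treating T4 and T6 results as independent to reach a higher figure would not be justified either. This objection succeeds, so multiplicity is conditional support only.

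**Low power is not zero power.** A reader might infer that mediation could never be detected. With very large assumed paths the joint test reaches 0.56. What is missing is the ability to interpret the result.

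**The third aim.** It is tempting to extend the criticism to effect modifiers, but Objectives says only "The third aim is to investigate if responses to memantine could be modulated by variables such as gender, symptoms subtypes". That is an intention to look, not a confirmatory claim, and it is no part of this point.

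**Conclusion.** The point holds for the mechanistic claim. One cognitive assessment on treatment, concurrent with the outcome and made in 20 patients, cannot decide between a direct antiobsessive action and one that works through attention. The schedule part of this follows from the protocol's own visit plan and needs no assumption.

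The size part rests on stated inputs: 10 per arm, no dropout, two-sided .05, and either the plan's f = 0.25 with correlation 0.5 or the standardised differences shown. Power for a cognitive effect is then 0.56 to 0.65 on the plan's own terms, and 0.19 to 0.40 for an unadjusted T4 difference of 0.5 to 0.8 SD. Absence of a significant cognitive effect would therefore be weak evidence of no effect. The mediation powers and the 23% to 46% false-positive range depend on assumed paths and correlations and are illustrations.

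The primary Y-BOCS comparison is not affected. This is a correction that should be made to a headline secondary claim, not a flaw in the main analysis.

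**What to change.** - In the abstract's Conclusions and the Discussion's Conclusion, replace the verb test with explore, and withdraw the conclusion that memantine is either directly antiobsessive or only imitates such an effect.
- For the second aim, name one attention measure already in the battery, for example the Trail Making Test. Compare it between arms at T4, adjusted for its screening value.
- Report the remaining cognitive measures as estimates with confidence intervals.
- Describe any analysis linking attention to Y-BOCS as an association, stating that the two were measured together at T4 and that direction cannot be inferred.

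No visits, patients or procedures are added. The cost is one fewer headline secondary claim.
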